### 2.8. Psychometric Assessment

The assessments will be carried out by a trained psychologist. The CSSRS [34] will be used to measure suicidal behavior and suicidal ideation. Sociodemographic data will also be collected, and a satisfaction survey will be carried out.

### 2.9. Implicit Association Test

The Spanish versions of the SI-AT and D/S-IAT [39] will be administered. These are 5 min tests administered by computer. The D-S IAT requires participants to match words from the following two semantic fields: “death” (die, dead, deceased, lifeless, and suicide) and “life” (alive, survive, live, thrive, and breathing). The attributes “me” (I, myself, my, self, and mine) and “not me” (they, them, their, theirs, and other) are used to categorize the words. The reaction times are processed using the standard D algorithm for IATs [40]. The algorithm takes into account the reaction time for the implicit association with death (faster reaction scores positively) and the reaction time for the implicit association with life (faster reaction scores negatively). Therefore, a participant with an unconscious bias towards life will have a negative score and a person with an unconscious bias towards death will have a positive score. The greater the score, the stronger the association in one direction or the other. A similar principle is applied for the SI-IAT, albeit using semantic fields related to self-harm. 

### 2.10. Ecological Momentary Assessment 

Digital monitoring will be carried out using the EMA methodology via the MEmind app. This app offers daily short questions that appear on the smartphone screen. Each day, a notification will appear with 2–4 random questions, which will appear at a random time during the day (from 9 a.m. to 9 p.m.) and which are part of a pool of 33 questions that make up the questionnaire. 

This questionnaire is based on the Salzburg Suicide Process Questionnaire (SSPQ) [41], the Patient Health Questionnaire-9 (PHQ-9) [42], the Positive and Negative Affect Schedule (PANA) [43], the Interpersonal Needs Questionnaire (INQ) [44], and previous EMA studies [45,46,47,48]. 

Questions will remain as a notification on the screen until they are answered. The application also has a free text field in which the participant can write comments on their status.

The EMA questions belong to six categories:Suicidality: 4 questions;Non-suicidal self-injury: 2 questions;Affect: 9 questions;Interpersonal experiences: 11 questions;Sleep: 4 questions;Apetite and eating: 3 questions.

The complete list of Ecological Momentary Assessment (EMA) questions can be found in Appendix A.

The digital safety plan is incorporated into the MEmind app and consists of a set of personalized coping strategies that the participant can use in the event of a suicidal crisis [20]. The original safety plan was designed by Stanley and Brown (2012) [20] and has been proven in several studies to decrease the risk of suicide [21]. 

It should be designed with the help of clinical staff. The safety plan will take advantage of smartphones by offering participants the ability to call loved ones, show relaxation videos, activate pre-recorded messages, link to websites with health resources, or connect the participant to emergency resources. During the first visit, the safety plan will be customized with the participant based on their personal preferences (e.g., by providing a list of emergency contacts or programming the app to trigger a song, image or video pre-selected by the participant).

The tabs of the safety plan are: 

The security plan consists of 7 tabs. In each tab, the patient can add text messages, voice messages, audios, photos, videos and links to websites.

The 7 tabs in the security plan are as follows:

1. Warning Signs—warning signs (thoughts, images, moods, situations, behaviors, etc.…) that may indicate a crisis is occurring.

2. Internal coping strategies—suggestions for distracting activities that participants can do on their own or without contacting another person (relaxation techniques, physical activityEtc.).

3. External coping strategies—suggestions for distracting activities that can be achieved with the help of the social environment.

4. Personal contacts—list of people in the participant’s support network. Only contacts can be added.

5. Professional contacts—professionals or institutions to contact during a crisis.

6. Safe environment—recommendations for making the environment safe.

7. Reasons for living—an important reason why life is worth living. For example, the participant could include a photograph (see Figure 2).

Apart from configuring the safety plan according to the individual needs of each participant, these tabs can be adapted to both the prevention of a suicide attempt and the prevention of self-harm. Thus, the warning signs can refer to both signs of an impending self-harm crisis and a suicidal crisis, while the safe environment can refer to both lethal-free and sharps-free, depending on the needs of each participant at each point in his or her evolution. The safety plan is multipurpose and can be tailored to each participant’s personal circumstances, providing a customized intervention. In addition, pre-loaded recommendations specific to NSSIs are included in the plan (explained below).

The different tabs contained in the MEmind safety plan are shown in Figure 3. 

Module of recommendations for the management of an NSSI crisis

In addition, the MEmind app includes a set of pre-installed recommendations for managing an NSSI crisis designed for young people. These recommendations include sections on ‘Identifying triggers’, ‘Strategies to use’, ‘Relaxing the five senses’ and ‘Stop’ (a series of intense stimuli that can act as a substitute for self-harm). 

### 2.11. Assessments: Questionnaires 

The assessments will be conducted by psychologists and/or psychiatrists, except for the screening in schools, which will be self-administered and carried out by the participant. All questionnaires will be completed in the MEmind collection portal, which allows for easy completion and immediate uploading to databases. 

The screening will consist of the completion of the following two short scales: Paykel Suicide Risk Scale [36];Inventory of Statements about Self-Injury scale (ISAS) [37].

The following questionnaires and instruments will be used for the assessment of items related to suicidal behavior and suicide ideation:Sociodemographic data including gender, age, family socioeconomic status, grade repetition, sexual orientation, number of siblings (including the participant) and child adoption.The Columbia Suicide Severity Rating Scale (CSSRS) [34] will be administered to measure suicide ideation and behavior. This scale will be employed both in the basal and the follow-up appointments.In addition, we will verify suicide attempts and suicide deaths through the digital medical record (clinical events).The Inventory for Depressive Symptomatology—Clinical (IDSC-30) scale [49] will be administered in order to measure depressive signs and symptoms.MacLean Screening Instrument for Borderline Personality Disorder [50].The Spanish version of the Death/Suicide Implicit Association Test (D/S-IAT) [38]Satisfaction surveys (one qualitative and one quantitative satisfaction survey).

The quantitative survey consists of the following questions, which participants will rate from 1 to 10:

1. Please rate your overall satisfaction with the application.

2. Is the application easy to use? 

3. Is the performance of the application good (speed of navigation, accuracy, lack of errors...)?

4. How do you rate the quality of the graphics?

5. How secure is the application with regard to the processing of personal data?

6. To what extent does the application have a clinical benefit? 

7. Would you be willing to recommend this application to family or friends?

The qualitative survey will ask the participant to comment on how their participation in the project has been, what aspect they liked most, what aspect they liked least and what suggestions they have for improvement, as well as any additional comments they may wish to make. 

Both surveys will be carried out at the six-month visit. 

Finally, participation and retention rates will be calculated.

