Here, we present the SmartCrisis-Teen study protocol, a Randomized Clinical Trial whose main objective is to evaluate the effectiveness of a digital safety plan combined with EMA to prevent suicidal behavior and NSSIs in the adolescent population. Our secondary objectives are to determine the feasibility and acceptability of the safety plan and to validate the use of the D/S IAT and SI IAT with respect to the gold standard Columbia Suicide Severity Rating Scale (CSSRS) [34]. Our hypothesis, based on previous studies carried out in the adult population [35], is that there will be a significant reduction in suicidal behavior and NSSIs episodes after the follow-up, which will be translated in lower scores in the CSSRS. As a secondary hypothesis, we expect that the digital safety plan will be feasible and well-accepted and that the D/S IAT and SI IAT will demonstrate adequate external and internal validity.

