### 2.7. Randomization and Follow-Up

A 1:1 randomization will take place after enrollment, where each participant will be assigned to one of the two groups. In both the control and intervention groups, an initial visit will take place during which a psychiatrist or psychologist will install the MEmind app on the participants’ mobile phone so that they can answer the questionnaires contained in the app with the guidance of the evaluator. In the case of self-administered questionnaires, the participants will answer directly on the screen of their mobile phone. In the case of hetero-administered questionnaires, the evaluator will complete them via the MEmind web portal, which is synchronized with the application.

Participants will be followed for six months, with weekly and monthly telephone visits and face-to-face visits at three and six months. In the intervention group, participants will also be given access to the safety plan included in the MEmind application. During the baseline visit, the plan will be set up for the first time and how it works will be explained. 

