### 2.12. Assessment Criteria

After six months, a before-and-after comparison will be made in both the control and intervention groups. 

Our main outcome will be a reduction in suicidal behavior, as measured by a score on the CSSRS.

Our secondary outcomes will be as follows: The occurrence of suicidal behavior as a clinical event (completed suicide, attempted suicide, ED visit for suicidal ideation, ED visit for self-harm),Predictive validity of the D/S IAT and SI IAT tests to clinical events recorded during follow-up.Acceptability of the project through user-perceived satisfaction.Project feasibility measured by participation and retention.

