### 2.13. Statistical Analysis

Traditional statistical analyses will be performed using SPSS 25.0 statistical software. For continuous variables, we will use t-tests to compare means between groups and ANOVA for multiple group comparisons. For categorical outcomes, chi-square tests will be employed to examine the frequency distributions.

In order to compare suicidal behavior (CSSRS score) at baseline and at the end of follow-up, a Wilcoxon test will be used. Survival curves (time to a new event, defined as a completed suicide, a suicide attempt or a visit to the emergency room for suicidal ideation) will be calculated using the Kaplan–Meier actuarial method.

To assess the feasibility of the project, the participation rate and retention (by percentage and by survival curve using drop-out as an event) will be calculated. To assess the acceptability of the project, descriptive statistics will be provided for the quantitative satisfaction survey and a content analysis will be conducted for the qualitative satisfaction survey. Binary logistic regression will be used to explore the correlation between the study variables, obtaining crude ORs adjusted for age and sex. 

Additionally, to reduce the probability of bias, we will factor by certain variables that could potentially act as confounders, such as the presence of other health apps in the users’ phones and response latency (which will be measured). 

All tests will be two-tailed, with a significance level of *p* < 0.05 and 95% confidence intervals.

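### Acceptability of the safety plan is a secondary objective, but no listed survey question asks about the plan, and the acceptability summary is not tied to the arm that receives it

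*Protocol article*

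**What the plan says.** **Objective and hypothesis (section 1).** The article states: "Our secondary objectives are to determine the feasibility and acceptability of the safety plan". The secondary hypothesis has the same object: "we expect that the digital safety plan will be feasible and well-accepted".

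**Outcome (section 2.12).** The matching secondary outcome is "Acceptability of the project through user-perceived satisfaction".

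**Analysis (section 2.13).** "To assess the acceptability of the project, descriptive statistics will be provided for the quantitative satisfaction survey", with a content analysis of the qualitative survey. No arm is named.

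**Instruments (section 2.11).** Seven questions, each rated 1 to 10, are presented as making up the quantitative survey. The first is "Please rate your overall satisfaction with the application" and the sixth is "To what extent does the application have a clinical benefit". On the other instrument: "The qualitative survey will ask the participant to comment on how their participation in the project has been", followed by what they liked most and least, suggestions and further comments. Both surveys take place at the six-month visit.

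**Exposure (sections 2.1 and 2.7).** Every participant has the MEmind app and its EMA. "In the intervention group, participants will also be given access to the safety plan included in the MEmind application". Allocation is 1:1.

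**Other plan-related information.** Section 2.4 foresees a review covering app use, interaction with the plan and satisfaction with the intervention. The Treatment as Usual subsection describes a control panel that also tracks plan activations.

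**The concern.** The objective concerns the randomised component, which one arm has. The outcome, its analysis and the listed questions concern the app or the project, which both arms share. The object of measurement therefore changes between the objective and the data.

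The app is not a ready stand-in for the plan. Section 2.10 describes EMA prompts that arrive every day and stay on the screen until answered, whereas the plan is meant for moments of crisis. An intervention participant who scores the app may be scoring mainly the prompts. A good score could then be read as acceptance of the plan when it reflects easy prompts, and a poor score could hide a plan that users valued.

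Section 4 expects good acceptance to show in the satisfaction surveys, so these surveys are the intended evidence. A question not put at the six-month visit cannot be recovered in the analysis.

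**Working it through.** No figure in the article bears on this point, so there is none to reproduce. The check compares the wording and counts the items.

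**Step 1: object named at each stage.**
- Objective and hypothesis (section 1): the safety plan.
- Outcome (section 2.12): the project.
- Analysis (section 2.13): the project.
- Quantitative survey (section 2.11): the application.
- Qualitative survey (section 2.11): participation in the project.

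The plan appears at the first stage only.

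**Step 2: item count for the quantitative survey.**
- Items naming the application: overall satisfaction, ease of use, performance, data security, clinical benefit, willingness to recommend = 6.
- Item on the graphics, with no object named: 1.
- Items naming the safety plan: 7 − 6 − 1 = 0.

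**Step 3: who can rate the plan.** Section 2.3 gives 120 × 9 = 1080 participants. At 1:1 this is 1080 / 2 = 540 per arm, so 540 / 1080 = 50% have no access to the plan. These are planned numbers. The share among actual respondents depends on who attends at six months in each arm.

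**Step 4: what the app ratings can show.**
- Control-arm mean: satisfaction with the app containing EMA without the plan.
- Intervention-arm mean: satisfaction with the app containing EMA and the plan together.
- Intervention mean minus control mean: the change in app satisfaction when the plan is added, among those who answer at six months.

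None of these is a rating of the plan. The difference comes closest, but it is a contrast and not a level. Suppose, as an assumption, that both arms average 7. The difference is 7 − 7 = 0. That is compatible with a plan its users liked about as much as the rest of the app, and also with a plan they hardly noticed.

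**Step 5: whether another described source fills the gap.**
- Open questions: an intervention participant may mention the plan, but nothing prompts for it.
- Control panel and interaction review: these may give use data. Section 2.12 defines acceptability as perceived satisfaction, which is a different quantity.
- Satisfaction with the intervention (section 2.4): announced, but the only satisfaction instruments described are those in section 2.11, and they contain no question on the plan.

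**The case against.** The strongest reply has four parts.

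1. **Pooling is not stated.** A reader might infer from section 2.13 that satisfaction will be averaged over both arms, so that half of the weight comes from people who never had the plan and the mean misses the intervention-arm mean by half of the arm difference. The text does not support this. It names no arm, pooled or separate, and a by-arm table is something an article commonly leaves to the full protocol or the analysis plan. That calculation holds only under pooling and needs an arm difference that the article does not give. This part of the reply stands, and no such bias is claimed.

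2. **Plan-related information is collected.** A reader might also infer that the surveys ask about nothing but the app. The open questions leave room for comments on the plan, and the section 2.4 review and the control panel bear on its use. This stands too, but use and unprompted remarks are not a measure of satisfaction with the plan.

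3. **The control ratings are useful.** Because both arms have EMA through the same app, the randomised difference in app ratings reflects what the plan adds, subject to dropout. This stands in part. It is good supportive evidence, but Step 4 shows why it does not give the level of acceptability.

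4. **The intervention may be the package.** Section 1 describes the trial as evaluating a safety plan combined with EMA, so intervention-arm app ratings could be read as rating that package. This is a fair reading of the main objective. The acceptability objective and hypothesis, however, name the safety plan alone.

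None of the four supplies a question on the plan, and neither would a by-arm table.

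**Conclusion.** The point holds as a mismatch between objective and measurement. The acceptability objective and hypothesis concern the safety plan, the outcome and analysis concern the project, 0 of 7 quantitative items ask about the plan, and the qualitative questions are open ones about taking part. App ratings, even within the intervention arm, do not directly measure acceptability of the plan, and the summary is not tied to the arm that receives it.

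The severity is minor. The outcome is secondary and descriptive, and the primary comparison is unaffected. The conclusion assumes that section 2.11 gives the surveys in full, as its wording indicates for the quantitative one, and that both arms complete them, since no restriction is stated. It does not depend on whether the arms are pooled.

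**What to change.** **Preferred change.**
- Section 2.11: add one or two 1–10 items on the safety plan (for example, how useful it was and how easy it was to use) and one open question on it, shown to the intervention arm only.
- Sections 2.12 and 2.13: define acceptability of the safety plan as the intervention-arm result on those items. Report the seven existing items by arm, with the control arm read as acceptability of the app with EMA, and give the between-arm difference as supportive information.

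**Alternative.** If the survey cannot be changed, restate the objective and hypothesis in section 1 as acceptability of the app or project, so that they match sections 2.12 and 2.13.

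**Cost.** Two or three extra questions in an electronic survey and a line or two of text. The downside is a slightly longer survey in one arm. The new items help only participants who have not yet had their six-month visit, so the change should be made early.

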### 2.12. Assessment Criteria

After six months, a before-and-after comparison will be made in both the control and intervention groups. 

Our main outcome will be a reduction in suicidal behavior, as measured by a score on the CSSRS.

Our secondary outcomes will be as follows: The occurrence of suicidal behavior as a clinical event (completed suicide, attempted suicide, ED visit for suicidal ideation, ED visit for self-harm),Predictive validity of the D/S IAT and SI IAT tests to clinical events recorded during follow-up.Acceptability of the project through user-perceived satisfaction.Project feasibility measured by participation and retention.

#### Treatment as Usual (TAU)

Likewise, participants who were previously followed-up will receive their usual treatment (TAU). This will be the psychiatric follow-up (scheduled appointments with the referring psychiatrist/psychologist) in the outpatient clinics for children and adolescents. This approach ensures that the well-being of participants is maintained in accordance with the standards applied to other patients receiving treatment within the national health system.

A continuous quality control phase will be implemented throughout the process to minimize data loss, ensure correct data collection and enable the resolution of any technical issues that may arise with the application. A control panel will be created to facilitate the monitoring of technical incidents, the information collected and the activation of safety plans.

### 2.13. Statistical Analysis

Traditional statistical analyses will be performed using SPSS 25.0 statistical software. For continuous variables, we will use t-tests to compare means between groups and ANOVA for multiple group comparisons. For categorical outcomes, chi-square tests will be employed to examine the frequency distributions.

In order to compare suicidal behavior (CSSRS score) at baseline and at the end of follow-up, a Wilcoxon test will be used. Survival curves (time to a new event, defined as a completed suicide, a suicide attempt or a visit to the emergency room for suicidal ideation) will be calculated using the Kaplan–Meier actuarial method.

To assess the feasibility of the project, the participation rate and retention (by percentage and by survival curve using drop-out as an event) will be calculated. To assess the acceptability of the project, descriptive statistics will be provided for the quantitative satisfaction survey and a content analysis will be conducted for the qualitative satisfaction survey. Binary logistic regression will be used to explore the correlation between the study variables, obtaining crude ORs adjusted for age and sex. 

Additionally, to reduce the probability of bias, we will factor by certain variables that could potentially act as confounders, such as the presence of other health apps in the users’ phones and response latency (which will be measured). 

All tests will be two-tailed, with a significance level of *p* < 0.05 and 95% confidence intervals.

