### 2.3. Sample Size Calculation

Sample size calculation will be performed using G*Power software, version 3.1. Based on previous clinical trials that explore the ability of interventions in SI reduction, in the midterm [36] we estimate an effect size of 0.5. Since the alpha error is set at 5% and the power at 95%, performing the modality “Means: Difference from constant (one sample case)”, the program determined that we would need a minimum of 45 participants per branch. Considering our recruitment capacity and assuming dropouts, we set the sample size at 60 participants per branch (120 in total). In order to stratify by center—so that we can explore the possibility of bias by different recruitment centers—we will try to have this sample size in each of the participating hospitals as well as in the educational contexts, which would result in a total sample of 120 × 9 = 1080 participants.

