## 3. Limitations

This study incorporates several methodologies to address potential biases, though inherent limitations remain. The digital nature of our intervention may introduce skewness when compared to traditional clinical interviews. We plan to mitigate this by employing statistical controls such as covariance analysis to adjust for baseline differences. 

Furthermore, while randomization reduces selection bias, the possibility of non-random dropout exists, which could lead to attrition bias. We will employ intention-to-treat analysis to minimize the effects of dropout. Despite these efforts, some external factors influencing participant engagement with the digital tool may not be fully controllable. We acknowledge these limitations and will discuss their potential impact on our findings, aiming to provide a transparent and critical assessment of our study’s results.

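### Sections 2.13 and 3 disagree on whether the between-arm CSSRS comparison is adjusted for baseline; the unadjusted tests of 2.13 would be valid but would waste a baseline score already collected.

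*Protocol article*

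**What the plan says.** The main outcome (section 2.12) is a reduction in suicidal behaviour measured by a CSSRS score, with a before-and-after comparison in each group. Section 4 expects lower CSSRS scores in the intervention group, which is a between-arm claim. The score is available at both ends of follow-up (section 2.11): "This scale will be employed both in the basal and the follow-up appointments".

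Section 2.13 contains four statements that bear on the analysis:

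- For between-group comparisons: "For continuous variables, we will use t-tests to compare means between groups and ANOVA for multiple group comparisons". No covariate is attached.
- For the CSSRS by name: a Wilcoxon test of baseline against end of follow-up.
- A logistic regression with age and sex as the only named adjusters.
- A plan to factor by possible confounders, with other health apps and response latency as the examples. Baseline CSSRS is not among them.

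Section 3 says that skewness arising from the digital nature of the intervention will be mitigated by "employing statistical controls such as covariance analysis to adjust for baseline differences". It does not name the CSSRS, and 2.13 does not take it up.

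Section 2.3 sizes the trial at 60 per branch and repeats that size over nine centres or settings, for 1080 participants in total. The stated reason for the repetition is to explore bias between recruitment centres.

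**The concern.** Taken alone, section 2.13 leads to an unadjusted between-arm comparison of the CSSRS; section 3 points to an adjusted one. A reader cannot tell which applies to the main outcome.

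The reason that section 3 gives does not help. Adding a baseline covariate removes outcome variance that baseline explains. It does not correct a skewed distribution or an effect of digital versus interview format.

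What is at stake is precision. The pooled sample mixes patients with a suicide attempt or self-injury in the previous month (section 2.2.1) with students who screened positive (sections 2.2.2 and 2.2.3). Baseline severity plausibly varies a good deal and predicts the six-month score. Leaving it out gives a wider interval for the safety-plan effect than the collected data allow.

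**Working it through.** **Inputs from the protocol article**

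- Section 2.3: "we estimate an effect size of 0.5"; alpha 5%, power 95%; one-sample comparison with a constant; "we would need a minimum of 45 participants per branch"; 60 per branch after allowing for dropout; 9 × 120 = 1080 in total.
- Section 2.7: 1:1 allocation, so 540 per arm when pooled.
- Section 2.13: two-tailed tests at 0.05.

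**Assumptions, not in the document**

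- rho, the correlation between baseline and six-month CSSRS; 0.3 to 0.7 is shown.
- The 0.5 is read as a between-arm difference in SDs of the six-month score. The protocol uses it only in a one-sample calculation.
- Normal-theory variance, although the score may be skewed.

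**Step 1. The plan's own figure.** A one-sample t-test with effect 0.5, alpha 0.05 and power 0.95 (noncentral t) gives n = 45 one-sided (power 0.951), which matches. Two-sided it gives n = 54. So 45 reproduces only as a one-sided, one-sample figure and says nothing about the power of a between-arm test. That is a separate issue.

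**Step 2. Effect of adjustment on variance.** ANCOVA multiplies the outcome variance by 1 − rho² and the interval width by √(1 − rho²).

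| rho | variance reduction | width ratio | interval narrower by |
|---|---|---|---|
| 0.3 | 9% | √0.91 = 0.954 | about 5% |
| 0.5 | 25% | √0.75 = 0.866 | about 13% |
| 0.7 | 49% | √0.51 = 0.714 | about 29% |

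**Step 3. Pooled sample, 540 per arm.** At d = 0.5, power exceeds 0.999 with or without the covariate. The gain is the narrower interval of step 2. Power would be at stake only for a much smaller pooled effect. As an illustration, d = 0.15 and rho = 0.5 gives 69% unadjusted and 81% adjusted.

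**Step 4. One centre or setting, 60 per branch.** Noncentral-t power, two-sided 0.05:

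- Unadjusted: noncentrality d√(n/2) = 0.5 × √30 = 2.74 on 118 df, power 77.5%.
- ANCOVA: effect d/√(1 − rho²) on 117 df.
- Change score: variance factor 2(1 − rho), effect d/√(2(1 − rho)) on 118 df.

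| rho | unadjusted | ANCOVA | change score |
|---|---|---|---|
| 0.3 | 77.5% | 81.3% | about 63% |
| 0.4 | 77.5% | 84.2% | about 70% |
| 0.5 | 77.5% | 88.0% | 77.5% |
| 0.6 | 77.5% | 92.4% | 85.9% |
| 0.7 | 77.5% | 96.7% | 93.9% |

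If dropout leaves 45 per branch, unadjusted power is 65.0%; ANCOVA gives 69.1%, 77.3% and 90.7% at rho 0.3, 0.5 and 0.7.

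A change score gives no gain at rho 0.5, loses below it, and above it recovers part of what ANCOVA gains.

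**The case against.** A reader might infer that the trial gives up about 10 points of power. The documents do not support that. The figure needs rho = 0.5, which the protocol does not state, and it applies to a single centre or setting. No section makes single-centre CSSRS comparisons confirmatory; the per-centre size serves to explore centre bias. Within one centre rho may also be lower than in the pooled sample, because the contrast between patients and students is then largely absent and entry is restricted by severity.

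A reader might also infer that baseline adjustment is missing from the plan, or that it would be done only if an imbalance were seen. Neither holds. Section 3 mentions adjustment, loosely, and does not make it conditional on an observed difference.

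Three further objections stand in part:

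- Applying the t-test sentence to the CSSRS is an inference, since the named CSSRS test is the baseline-to-end Wilcoxon. But section 4 expects a between-arm difference, and the between-group tests that 2.13 offers for continuous variables have no baseline term.
- The main outcome is worded as a reduction, so a change score is a natural reading. It recovers much of the gain when rho is well above 0.5 and none at or below 0.5.
- Covariate lists are commonly left to an analysis plan. That would excuse silence. It does not excuse two sections that point in different directions, or a remedy that does not address the problem it is given for.

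**Conclusion.** The point holds as an inconsistency with a cost in precision. Sections 2.13 and 3 do not agree on whether the between-arm CSSRS comparison is baseline-adjusted, and section 3 credits covariance analysis with repairing digital-format skewness, which it cannot do. An unadjusted comparison would remain valid under randomisation, so no bias is claimed.

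For the planned total of 540 per arm, the loss is an interval wider than it need be: adjustment would narrow it by about 5% to 29% for rho from 0.3 to 0.7, with power at d = 0.5 about 100% either way. In a single centre or setting of 60 per branch, adjustment would add about 4 to 19 points of power over the same range. All these figures rest on the assumed rho and normal-theory variance; the power figures also rest on reading 0.5 as a between-arm effect. The change is worth making because it is free, not because the trial depends on it.

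**What to change.** In section 2.13, state that the between-arm CSSRS comparison is an ANCOVA (linear model) of the six-month score on arm, with baseline CSSRS as a covariate for all participants. If the score is strongly skewed, use a rank-based ANCOVA or a proportional-odds model with the same covariate.

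In section 3, refer to that model and drop the claim that covariance analysis mitigates skewness from the digital format.

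The cost is a few lines of text and one extra model term in SPSS, with no new data, visits or participants.
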